## Abstract

**Introduction:**

Undiagnosed fatty liver disease is prevalent in the community, due to high rates of harmful alcohol consumption and/or obesity. Fatty liver disease can progress to cirrhosis and its complications. Early identification of liver disease and treatment may prevent progression to cirrhosis. Biomarkers including FIB-4, enhanced liver fibrosis (ELF), PRO-C3 and vibration controlled transient elastography (VCTE) can stage liver fibrosis, but it is not known how well they perform in a primary care population. Moreover, no assessment of long-term prognostic ability of these biomarkers has been conducted in primary care. We aim to evaluate the performance of fibrosis biomarkers in primary care to develop a pathway to detect advanced fibrosis.

**Methods and analysis:**

This prospective, observational cohort study will recruit 3000 individuals with fatty liver disease risk factors (obesity, type 2 diabetes or hazardous alcohol consumption) at their primary care ‘annual chronic disease review’. Participants will have a ‘liver health check’. Two pathways will be evaluated: (1) all have FIB-4, ELF and VCTE performed, and (2) patients have an initial assessment with FIB-4 and ELF, followed by VCTE in only those with increased FIB-4 and/or ELF. Individuals with suspected significant/advanced liver fibrosis (liver stiffness measurement>8 kPa), will be reviewed in secondary care to confirm their fibrosis stage and institute treatment. The performance of FIB-4, ELF, PRO-C3, VCTE and novel biomarkers alone or in combination for advanced fibrosis/cirrhosis will be evaluated. Participants will be followed longitudinally via their electronic health records to assess long-term clinical outcomes.

**Ethics and dissemination:**

Ethical approval was obtained from the London-Chelsea Research Ethics Committee (22/PR/0535; 27 June 2022). Recruitment began on 31 October 2022. Outcomes of this study will be published in peer-reviewed journals and presented at scientific meetings. A lay summary of the results will be available for study participants and will be disseminated widely by LIVErNORTH.

What is already known on this topicUndiagnosed fatty liver disease is highly prevalent in the community, primarily due to high rates of alcohol consumption and obesity. The optimum approach to identify individuals with advanced fibrosis in the community remains unknown.What this study addsThis study will evaluate the performance of current and novel biomarkers to detect advanced liver fibrosis among patients at increased risk of fatty liver disease in primary care to determine the most clinically and cost-effective approach.How might the study affect research, practice or policyThis study will evaluate the impact of a liver fibrosis detection pathway in primary care and develop the most clinically and cost-effective pathway for widespread implementation or further study in a large randomised trial.

## Introduction

Undiagnosed fatty liver disease is highly prevalent in the community, primarily due to high rates of harmful alcohol consumption and/or obesity.^1^ Fatty liver disease can progress to cirrhosis and complications including liver failure and hepatocellular carcinoma. An estimated 1-in-5 individuals in the UK have non-alcohol-related fatty liver disease (NAFLD).^2^ Moreover, the prevalence of potentially harmful alcohol consumption is high in the community (15% females and 25% males in England) and alcohol accounts for 75% of deaths due to liver disease, costing the National Health Service (NHS) £3.5 billion per annum.^1^ The increasing prevalence of liver disease risk factors in the community and lack of recognition of liver disease are likely causes for the rising rates of cirrhosis and liver-related deaths.^1^

Because liver disease is usually asymptomatic at early stages, patients frequently present once end-stage liver disease has developed. One study showed that 73% of patients presenting with their first admission with cirrhosis or liver failure had never been referred to a liver clinic, which indicates a lack of early detection of liver disease.^1^ Importantly, most liver-related complications, mortality, healthcare costs and reduction in quality of life occurs in patients with cirrhosis rather than earlier stages of liver disease.^3 4^ Therefore, early identification of liver disease before cirrhosis and initiation of lifestyle changes may prevent progression to cirrhosis for some patients.^5^

Liver enzymes are often used in primary care to identify individuals with liver disease,^6^ but this approach is insensitive because up to 50% of patients with advanced liver fibrosis/cirrhosis have normal liver enzymes.^7^ Because stage of liver fibrosis is the key prognostic factor in liver disease,^8^ use of a test for fibrosis is likely to be far more efficient to identify advanced fibrosis. Therefore, taking a different approach and performing case finding using non-invasive tests to identify advanced liver fibrosis in individuals with liver disease risk factors may be an effective strategy.^9 10^

Numerous biomarkers have been proposed for the non-invasive staging of liver fibrosis.^11^ These include ‘indirect’ biomarkers, such as FIB-4 (age, AST, ALT and platelets),^12 13^ and ‘direct’ serum biomarkers that measure collagen matrix components, such as enhanced liver fibrosis ‘ELF’ test (hyaluronic acid, TIMP1 and P3NP)^14 15^ and more recently the novel collagen neo-epitope biomarker PRO-C3.^16 17^ In addition, vibration controlled transient elastography (VCTE; Fibroscan), an ultrasound-based technique that measures liver elasticity as a surrogate for fibrosis, has emerged as an effective non-invasive fibrosis test.^18^ As well as providing an accurate assessment of stage of fibrosis, these biomarkers can stratify patients for risk of liver-related events with reasonable accuracy.^19 20^

Current fibrosis biomarkers have advantages and disadvantages but the majority of data describing their performance is derived from secondary/tertiary care settings in patients with known liver disease (mainly NAFLD)^21^ and these tests have not been systematically evaluated in an unselected primary care population where their performance may be different. Therefore, an evaluation of their performance in a community ‘case finding’ setting is warranted. The FIB-4 score, which is effectively cost free, has been extensively evaluated in patients with NAFLD and can reliably exclude advanced fibrosis,^13 21^ but has a relatively high false positive rate for advanced fibrosis, particularly when used in individuals over the age of 65 years.^22^ Given this high false positive rate, a second-line confirmatory test is required.^6^ ELF has been evaluated in several liver diseases, including NAFLD and alcohol-related liver disease (ARLD).^23^ It performs reasonably well^15^ and has been used in a two-step fibrosis staging pathway after the FIB-4 for patients with raised liver enzymes in primary care, significantly improving the correct identification of advanced fibrosis compared with standard care.^24^ PRO-C3, the newest biomarker, has good performance for advanced fibrosis in NAFLD and ARLD.^16 17 25^ VCTE is now well established for staging liver fibrosis in patients with NAFLD and ARLD.^18 26 27^ Overall, a liver stiffness measurement (LSM) of <8 kPa reliably excludes advanced fibrosis/cirrhosis in patients with NAFLD and ARLD (sensitivity 93% and 94%, respectively), while an LSM of >12 kPa has 88% specificity for advanced fibrosis/cirrhosis in both ARLD and NAFLD.^26^ However, VCTE usually requires a specific attendance at a healthcare facility and needs to be performed by a trained operator, which could limit its use as a screening tool in primary care. VCTE also has a failure rate of approximately 5%, particularly among older patients (>60 years) and those with a Body Mass Index (BMI)>35 kg/m^2^.^28^

Recent evidence suggests that the diagnostic accuracy of blood fibrosis biomarkers may be different in a primary care population where the prevalence of advanced fibrosis is lower.^15 29^ Moreover, evaluation of the performance of liver fibrosis biomarkers has been cross-sectional and no assessment of long-term follow-up has been conducted to determine whether cases of advanced liver disease have been missed. Therefore, large-scale baseline and longitudinal assessment of the use of VCTE alongside other blood biomarkers to identify patients with advanced fibrosis in primary care is warranted.

## Aim

The overall aim of this study is to develop an effective pathway to identify patients with advanced liver fibrosis in individuals with risk factors for liver disease (obesity, type 2 diabetes (T2DM) or hazardous alcohol use) in primary care. The study will incorporate a ‘liver health check’ within primary care annual chronic disease reviews to identify advanced liver fibrosis. This pathway will be a platform to evaluate the performance of liver fibrosis biomarkers to develop the most clinically and cost-effective pathway for the early identification of advanced liver fibrosis in the community.

### Specific aims

To implement and assess the effectiveness of primary care-based risk-stratification pathways using VCTE and blood biomarkers to identify advanced liver fibrosis and predict outcomes among individuals with liver disease risk factors.To evaluate whether implementation of the pathways increases the diagnosis of patients with advanced fibrosis compared with standard care.To use the Stratification Of LIver Disease (SOLID) platform to assess the performance of novel and established fibrosis biomarkers and so determine the optimum biomarker strategy for wider implementation within the NHS.To assess the cost effectiveness of novel and established risk stratification pathways.To assess the acceptability of embedding the pathways into routine primary care chronic disease management to guide wider implementation.

## Methods and analysis

### Study design

SOLID is a prospective, observational cohort study where individuals with risk factors for fatty liver disease will have a liver health check to identify advanced liver fibrosis/cirrhosis when they attend their primary care annual chronic disease review. The diagnostic performance of fibrosis biomarkers for advanced fibrosis/cirrhosis with respect to long-term outcomes will be evaluated.

Primary care annual chronic disease reviews offer an ideal place to conduct a liver risk assessment since much of the information needed for this is already collected. Liver risk factors will be assessed, and individuals with obesity (BMI>30 kg/m^2^), T2DM or hazardous alcohol consumption (using Alcohol Use Disorders Identification Tool; (AUDIT score>8)) will have a ‘liver health check’ using established fibrosis biomarkers including FIB-4, ELF and VCTE. Blood samples will be taken for novel biomarkers, including PRO-C3, to evaluate their performance. Two pathways will be evaluated (figure 1): (1) all patients have FIB-4, ELF test and VCTE performed, and (2) patients have an initial assessment with the FIB-4 and ELF test, followed by VCTE in only those with increased FIB-4 and/or ELF.

**Figure 1 F1:**
[figure not shown]
An overview of the clinical assessment pathways for liver fibrosis in primary care. ALP, alkaline phosphatase; ALT, alanine aminotransferase; AST, aspartate aminotransferase; AUDIT, Alcohol Use Disorders Identification Tool; ELF, enhanced liver fibrosis test; GGT, gamma glutamyl transferase; LSM, liver stiffness measurement; T2DM, type 2 diabetes; VTCE, vibration controlled transient elastography.

Irrespective of which pathway a patient is recruited into, individuals with suspected moderate or advanced liver fibrosis (LSM>8 kPa), will be reviewed in secondary care to confirm their stage of liver fibrosis and institute specific treatment and/or enhanced lifestyle management depending on the underlying diagnosis within routine NHS clinical services.^30 31^ When cirrhosis is identified, patients will be entered into liver cancer and varices surveillance programmes according to current standard of care.^32^

These pathways will allow us to evaluate the diagnostic accuracy of FIB-4, ELF, PRO-C3, VCTE and novel biomarkers alone or in combination for advanced fibrosis/cirrhosis in individuals with risk factors for liver disease. Unique to this study, participants will also be followed longitudinally via their electronic health records and NHS Digital to assess long-term clinical outcomes.

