### Study outcomes

#### Primary outcome

The primary outcome of SOLID is to assess the number of patients identified with advanced liver fibrosis/cirrhosis using each of the pathways based on an overall clinical evaluation by a panel of hepatologists.

The presence of advanced fibrosis will be determined by an overall clinical assessment after secondary care review and will include all investigations undertaken in primary and secondary care. Where there is uncertainty about the stage of liver fibrosis, a liver biopsy will be offered as per usual clinical care. The overall clinical assessment for advanced fibrosis will be undertaken by three hepatologists. Where cases are equivocal, all the clinical data for these patients will be reviewed independently by each of the hepatologists to determine the presence of advanced fibrosis. An agreement analysis will be conducted to determine the concordance between hepatologists. Discrepancies will be resolved by consensus.

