### Study procedures

All participants will have a liver fibrosis assessment using established biomarkers (VCTE and/or FIB-4 and ELF), blood tests and relevant clinical and demographic data collected at the time of assessment, as shown in table 1.

The optimum clinical pathway for the evaluation of liver fibrosis is not known so we plan to evaluate two pathways (figure 1) to determine which is most clinically and cost-effective. In pathway one, all patients will be offered VCTE and have blood tests for liver fibrosis biomarkers. In pathway two, patients with FIB-4>1.3 and/or ELF>9.8 indicating possible advanced fibrosis/cirrhosis will have VCTE to stage fibrosis.

VCTE will be conducted by trained operators at Newcastle Hospitals or in the primary care centre depending on the proximity of primary care sites to the hospital (sites close to the hospital will have VCTE performed at the hospital and those further away will have it performed at the practice). LSMs and controlled attenuation parameter readings will be obtained using a Fibroscan 430 mini+machine with M or XL probe as per the manufacturer’s recommendations. VCTE reading will be considered ‘reliable’ if they meet the accepted quality criteria of at least 10 readings from the same location with a single probe and the IQR/median ratio is less than 30% when the LSM exceeds 7.1 kPa.^35^

Individuals will be given a report of their liver assessment (LSM or FIB-4/ELF) to indicate their stage of liver fibrosis. All participants will be given relevant lifestyle advice and an information booklet entitled ‘Looking after your Liver’ (online supplemental file 1).

10.1136/bmjgast-2022-001092.supp1Supplementary data

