Individuals with an LSM<8 kPa or who have low FIB-4/ELF (pathway 2), which excludes advanced fibrosis, will remain in primary care with further monitoring as per their usual care. Individuals with an LSM>8 kPa, indicating possible moderate to advanced liver fibrosis, will be referred to secondary care for further assessment and treatment. VCTE has a failure rate of approximately 5%. For individuals where it is not possible to obtain a reliable LSM, the ELF test and FIB-4 will be used as an alternative test to assess fibrosis. Both the FIB-4 and ELF tests can reliably exclude advanced fibrosis in patients with fatty liver disease.^13 14^ Individuals with a low ELF (<9.8) and FIB-4 score (<1.3) will be managed in primary care, while those with an ELF>9.8 and/or FIB-4 score>1.3 will be referred to secondary care for further assessment.

Individuals with raised liver blood tests will have investigations as per standard care following the Northeast and North Cumbria Abnormal Liver Blood Test Guidelines.^36^

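### VCTE is promised baseline diagnostic accuracy, but LSM decides who reaches the reference assessment, so its sensitivity at 8 kPa is about 100% by construction

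*Protocol article*

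**What the plan says.** The Protocol article treats VCTE as a test under evaluation in two places. The abstract (Methods and analysis) says "The performance of FIB-4, ELF, PRO-C3, VCTE and novel biomarkers alone or in combination for advanced fibrosis/cirrhosis will be evaluated", and the Study design text below Figure 1 says "These pathways will allow us to evaluate the diagnostic accuracy of FIB-4, ELF, PRO-C3, VCTE and novel biomarkers alone or in combination". The section on assessing biomarker performance then lists ROC analysis, sensitivity, specificity, predictive values and both likelihood ratios for each test or combination.

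The reference standard is given under Primary outcome: "The presence of advanced fibrosis will be determined by an overall clinical assessment after secondary care review and will include all investigations" from both primary and secondary care. Entry to secondary care is set by LSM in both pathways: "individuals with suspected moderate or advanced liver fibrosis (LSM>8 kPa), will be reviewed in secondary care to confirm their stage of liver fibrosis" (Study design), and again "Individuals with an LSM>8 kPa, indicating possible moderate to advanced liver fibrosis, will be referred to secondary care for further assessment and treatment" (Study procedures). Test negatives are not assessed: "Individuals with an LSM<8 kPa or who have low FIB-4/ELF (pathway 2), which excludes advanced fibrosis, will remain in primary care". Pathway 2 adds an earlier gate: "patients with FIB-4>1.3 and/or ELF>9.8 indicating possible advanced fibrosis/cirrhosis will have VCTE to stage fibrosis".

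The Secondary outcomes section describes the accuracy question differently. It names only blood-based markers as the tests and allows either the overall clinical assessment or LSM itself as the standard.

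**The concern.** A test's sensitivity can be estimated only if some of the people it calls negative also receive the reference assessment. Here the LSM result decides who is assessed, so a VCTE false negative has almost no way to be recorded. The panel also uses the LSM when it stages the patient, so the test forms part of its own yardstick.

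The Introduction says that performance in primary care may differ from secondary care and needs evaluating there. For VCTE sensitivity the design cannot show such a difference: the reported figure would be close to 100% whether VCTE missed few cases or many. That figure would then feed the choice of an optimum pathway for wider NHS use.

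**Working it through.** **Inputs.** N = 3000, about 1500 per pathway, prevalence 5%–7.5% (sample size section). VCTE at 8 kPa: "sensitivity 93% and 94%, respectively" for NAFLD and ARLD (Introduction). VCTE failure rate about 5% (Study procedures). Specificity at 8 kPa is not given; I assume 70%–95%.

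**1. The plan's own split.** 3000 × 0.05 = 150 and 3000 × 0.075 = 225 diseased; the remainders are 2850 and 2775. These match the stated 150–225 and 2775–2850. Because all 3000 are classified, the text implies that unreferred participants count as negative, although no rule says so.

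**2. Cases hidden in pathway 1.** Cases: 1500 × 0.05 = 75 and 1500 × 0.075 = 112.5. Missed = cases × (1 − sensitivity):
- 5% prevalence: 75 × 0.06 to 0.07 = 4.5 to 5.3
- 7.5% prevalence: 112.5 × 0.06 to 0.07 = 6.8 to 7.9

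**3. Reported against true values at 8 kPa, unreferred counted as negative.**
- Sensitivity: every recorded case has LSM > 8 kPa, so 100% is reported against 93%–94%.
- LR− = (1 − sensitivity)/specificity: 0 is reported; the true value is 0.06/0.95 = 0.06 to 0.07/0.70 = 0.10.
- NPV = TN/(TN + FN): 100% is reported. The lowest true value is 1387.5 × 0.70 = 971.25, then 971.25/(971.25 + 7.875) = 99.2%. The highest is 1425 × 0.95 = 1353.75, then 1353.75/(1353.75 + 4.5) = 99.7%.

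**4. The result does not respond to the truth.** If primary care sensitivity were 70%–80% (assumption), 75 × 0.20 = 15 to 112.5 × 0.30 = 33.8 cases would be missed and true NPV would be 96.6%–98.9%. The design would still report 100% for both.

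**5. Only verified participants analysed.** Nobody with a valid LSM below 8 kPa is in the table. Sensitivity is again 100%, specificity is 0/FP = 0, and NPV is 0/0.

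**6. Failed scans.** These are referred on ELF and FIB-4. If failures count as VCTE-negative and the serum markers detect 70%–90% of their cases (assumption), reported sensitivity is 0.8835/(0.8835 + 0.035) = 96% down to 0.8835/(0.8835 + 0.045) = 95%, where 0.8835 = 0.95 × 0.93. The true value is 88%–89%.

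**7. Higher cut-offs and ROC area.** At 12 kPa, sensitivity is inflated by 1/0.94 to 1/0.93: an assumed 70% reads 74%–75%. With unreferred counted as negative, AUC = specificity at 8 kPa + (1 − specificity) × AUC above 8 kPa. With 70% and 0.6 assumed, AUC = 0.70 + 0.30 × 0.6 = 0.88.

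**8. Serum markers.** In pathway 2 every recorded case has passed the FIB-4/ELF gate, so the either-positive rule has sensitivity of about 100% by construction. Single markers rise too: with 70% each and independent errors (assumption), 0.70/0.91 = 77%. In pathway 1 with VCTE sensitivity 93%, an assumed marker sensitivity of 80% reads 80% if errors are independent of VCTE. The bounds are (0.80 + 0.93 − 1)/0.93 = 78.5% and 0.80/0.93 = 86%.

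**The case against.** The strongest reply is that the protocol already treats VCTE as reference rather than competitor. The secondary accuracy outcome omits it from the tests, and the Strengths section calls it a key fibrosis endpoint. The Limitations section names the reference standard as the main weakness, and long-term follow-up is planned because earlier studies could not determine a miss rate. All of this is true. But the abstract and the Study design text still list VCTE as a test to be evaluated, so the document gives it both roles. The Limitations section concedes that biopsy in everyone is impossible; it does not mention LSM-gated verification or that the tests enter the standard. Follow-up events give prognostic evidence and do not establish stage at baseline.

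A second reply is that handling of unverified participants belongs in the analysis plan. The gate, the standard and the test list are fixed here, however, and neither way of handling them gives a usable sensitivity and NPV for VCTE at 8 kPa.

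A third reply stands in part. Other routes to investigation exist: failed scans are referred on serum markers, and raised liver blood tests lead to standard-care work-up. This is why the figure is about 100% and not exactly 100%.

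A reader might infer more than the text supports:
- VCTE's ROC area is not fixed near perfection, as step 7 shows.
- NPV is not seriously distorted at the protocol's own sensitivity.
- Serum markers are not favoured throughout. The by-construction effect is confined to the pathway 2 gate, and in pathway 1 verification alone need not favour them. FIB-4 and ELF do form part of the panel's information, but the size of that effect cannot be computed from the document.
- Panel access to PRO-C3 is not stated.

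**Conclusion.** The point holds at 8 kPa, the only LSM threshold on which the study acts. The design cannot estimate baseline VCTE sensitivity, LR− or NPV there. Sensitivity would be overstated by 6–7 percentage points at the protocol's own 93%–94%, and by more if VCTE does worse in primary care. The NPV shift is under one point at 93%–94%.

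The count of 5–8 hidden cases rests on three assumptions: unreferred participants are scored negative, the cited sensitivity carries over to primary care, and the prevalence applies to advanced fibrosis. The last is uncertain, because the sample size section gives 5%–7.5% first for moderate/advanced and then for advanced fibrosis.

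The primary outcome, a count of cases identified by each pathway, is not undermined by this point.

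**What to change.** Reconcile the abstract, the Study design text and the biomarker performance section with the Secondary outcomes by stating that VCTE is part of the reference standard. Then:

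- For VCTE, report failure rate, yield and the panel-confirmed proportion by LSM band, noting that the panel sees the LSM. Do not report or compare its baseline sensitivity, NPV, LR− or AUC.
- Do not report sensitivity or NPV of the FIB-4/ELF gate from pathway 2. Estimate serum-marker accuracy from pathway 1, labelled as relative to an LSM-gated standard.
- Use the 2-, 5- and 10-year liver-related events already being collected as the evidence on missed disease, described as prognostic and not as verification of baseline stage.

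This changes wording and reporting only; referral and care stay as they are. The cost is fewer headline accuracy statistics for VCTE, and serum-marker accuracy from about half the cohort (75–112 expected cases instead of 150–225), with intervals for sensitivity up to about √2 = 1.4 times as wide.
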